#### Intended Outcome Measures

##### Overview

Table 3 illustrates the framework for all study outcomes, including the instruments used to assess each variable. The details of the intended outcome measures for the interventions in the main study (RCT) are provided in subsequent sections.

**Table 3 table3:** Framework of the study’s outcome measures and instruments.

Variables	Instruments
Motor impairment	Fugl-Meyer Assessment for upper extremity
Motor function	Wolf Motor Function Test
Perceived motor function	Motor Activity Log
Upper limb self-efficacy	Upper Limb Self-Efficacy Test

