### Sample Size Calculation

We used the G*Power software (version 3.0.10; University of Düsseldorf) to calculate the required sample size. A mixed model ANOVA, a statistical method used to analyze the effects of interventions over time and between groups, was selected to analyze the interventions’ time, group, and interaction effects. The *F* test (ANOVA repeated measures within and between interactions), a specific type of statistical test used in the mixed model ANOVA, was selected for this analysis. With a study power of 80%, an α level of .05, and an effect size of 0.25 (based on the primary outcomes from a previous CIMT study [47]), a minimum sample size of 42 participants (14 in each group) is required. If a group has more than 14 eligible participants, the first 14 to provide consent will be recruited based on the referral date. This first-come, first-served approach ensures transparency in participant selection while maintaining cluster integrity.

An intention-to-treat analysis, which includes all randomized participants, regardless of their adherence to the protocol or completion of the study, will be implemented for this RCT. Under this approach, all recruited participants will be included in the final analysis regardless of protocol adherence, withdrawal, or discontinuation. For participants who withdraw or discontinue the treatment, their baseline data will be used as exit data in the primary analysis. This conservative approach acknowledges the potential impact of missing data while maintaining randomization integrity. Sensitivity analyses using multiple imputation techniques, which are statistical methods used to handle missing data, will be conducted to assess the robustness of findings against different missing data assumptions. This analytical strategy aligns with CONSORT guidelines for reporting randomized trials and addresses potential selection bias that might occur with complete-case analysis.

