### Statistical Analysis

Data will be analyzed using IBM SPSS Statistics software (version 29.0), adhering to the intention-to-treat principle, which includes all randomized participants regardless of protocol adherence. Participant characteristics and baseline measures will be summarized using descriptive statistics, including mean, SD, median, and IQR.

Before primary analyses, data will be assessed for normality using the Shapiro-Wilk test and homogeneity of variance using the Levene test. For outcomes meeting parametric assumptions, a 2-way mixed model ANOVA will be used to compare the effects of the interventions’ interactions between and within groups. Appropriate transformations or nonparametric alternatives will be applied in cases of violated parametric assumptions. Potential confounding variables, such as baseline motor function and stroke severity, will be included as covariates to provide adjusted treatment effect estimates. Statistical significance will be set at *P*<.05 for all analyses.

The linear mixed-effects models that include the center as a fixed effect covariate and random intercepts at the participant level will be used to address residual center-specific effects without invoking a design effect. This modeling framework accommodates hierarchical data structures in single-cluster designs while preserving valid inference for group-by-time interactions.

Missing data will be addressed using multiple imputation techniques, with sensitivity analyses comparing results to those obtained using the baseline observation carried forward method. This comprehensive approach ensures a robust interpretation of intervention effects while preserving statistical power.

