## Discussion

### Anticipated Findings

This study evaluates the effects of combining CIMT with NMES on UE function among chronic stroke survivors. We hypothesize that the combined CIMT+NMES intervention will produce superior improvements in motor function and perceived functional use compared to CIMT alone or conventional therapy. This dual approach leverages complementary mechanisms: CIMT addresses learned nonuse through intensive task practice [48], while the NMES facilitates muscle activation and enhances proprioceptive feedback to support voluntary movement.

We examined current rehabilitation paradigms for chronic stroke to contextualize our approach within existing evidence. CIMT has established efficacy for improving UE function in selected populations of individuals who have experienced a stroke through forced use and mass practice tasks [49]. Similarly, NMES demonstrates clear benefits for muscle strengthening and motor unit recruitment in paretic limbs [50]. However, a few studies have investigated their combined therapeutic potential [10]. Recent evidence indicates that multimodal rehabilitation approaches may amplify neuroplastic changes through synergistic cortical reorganization mechanisms. Functional magnetic resonance imaging studies have documented enhanced cortical activation patterns when peripheral electrical stimulation accompanies intensive motor training, suggesting accelerated neural adaptation compared to single interventions [21].

This study advances this emerging field by providing the first systematic comparison of combined CIMT+NMES therapy against established monotherapies. This investigation addresses a critical gap in stroke rehabilitation evidence, particularly for chronic stroke survivors who typically experience limited recovery with conventional approaches. By examining whether combined interventions overcome the ceiling effects often observed with single modalities, our findings will inform evidence-based treatment selection for this challenging population.

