### Clinical Implications and Future Directions

Our findings will directly inform clinical decision-making regarding optimal rehabilitation strategies for chronic stroke survivors with persistent UE deficits. Should the combined intervention demonstrate superiority, clinicians will gain evidence supporting integrated treatment protocols that maximize functional recovery potential. The comprehensive outcome battery, including motor function (FMA-UE), activity performance (Wolf Motor Function Test), perceived use (Motor Activity Log), and self-efficacy (UPSET), provides multidimensional insights into treatment effects across the International Classification of Functioning, Disability, and Health domains.

Future research should expand upon our foundation through several critical avenues. Large-scale multicenter trials incorporating cluster randomization with appropriate design effects will establish definitive efficacy estimates. Extended follow-up periods of 6 to 12 months will determine whether initial gains translate into sustained functional improvements. Neurophysiological assessments, including transcranial magnetic stimulation and electroencephalography, could elucidate the cortical mechanisms underlying potential synergistic effects [51].

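### No primary outcome is named and every analysis is tested at P<.05, so the success criterion is open and the four specified interaction tests carry about a 10–19% chance of a false positive

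*Protocol article*

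**What the plan says.** - **Threshold.** The Statistical Analysis section says: "Statistical significance will be set at *P*<.05 for all analyses". It gives no adjustment, ranking of outcomes or order of testing.
- **Outcomes.** Table 3 and the sections after it list four instruments without ranking. The MAL has two subscales. The only mention of primary outcomes, under Sample Size Calculation, concerns an earlier CIMT study that supplied the effect size. A primary analysis is mentioned there and under Statistical Analysis, without an outcome attached.
- **Planned test.** The trial is powered on the F test for "ANOVA repeated measures within and between interactions", and the analysis is described as "a 2-way mixed model ANOVA will be used to compare the effects of the interventions’ interactions between and within groups". No pairwise or post hoc test is named.
- **Hypothesis.** Anticipated Findings expects the combined arm to give "superior improvements in motor function and perceived functional use compared to CIMT alone or conventional therapy". The Results section speaks more broadly of upper-extremity function.
- **Label.** Table 3 sets motor function against the "Wolf Motor Function Test" and motor impairment against the FMA-UE. Clinical Implications and Future Directions instead has "motor function (FMA-UE), activity performance (Wolf Motor Function Test", and the FMA-UE section also says that this scale assesses motor function.
- **Reassurance.** Strengths and Limitations says that the mixed ANOVA guards against inflation of type I error.

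**The concern.** Two things are left open together. The first is which instrument tests the hypothesis. Because 'motor function' names two different scales, either could be presented afterwards as the intended test. The hypothesis also names perceived use, without saying whether both results are needed. The second is error across instruments. A single threshold applied to four unranked outcomes gives several chances of a nominally significant result, and nothing in the text says that one such result would be insufficient. The authors intend the findings to inform clinical decisions and practice guidelines, so a positive claim resting on whichever instrument crossed .05 would matter. A reader of Strengths and Limitations would also conclude, wrongly, that multiplicity has been dealt with.

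**Working it through.** **Inputs from the protocol.** "With a study power of 80%, an α level of .05, and an effect size of 0.25"; "a minimum sample size of 42 participants (14 in each group) is required"; three arms; two assessments (baseline and post-intervention); four instruments.

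**Assumptions not in the protocol.** Correlation between repeated measures ρ = 0.5 with sphericity, chosen because it returns the stated sample size. Common correlation between outcomes r from 0 to 0.9. Independent participants and valid individual-level tests.

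**1. Reproduce the planned sample size.** For the within-between interaction with k = 3 groups and m = 2 times:

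λ = f²·N·m/(1 − ρ) = 0.0625 × 42 × 2/0.5 = 10.5, with df₁ = (k − 1)(m − 1) = 2 and df₂ = (N − k)(m − 1) = 39.

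Power at α = .05 is 0.803, and 42 is the smallest multiple of three that reaches 0.80. The figure is reproduced, for one interaction test on one outcome.

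**2. Error over four interaction tests.** If the tests were independent: 1 − 0.95⁴ = 0.185. For correlated outcomes, change scores were simulated under no true differences (14 per arm, 40,000 runs for each r). The table gives the chance of at least one result at P<.05.

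| Family of tests | r = 0 | r = 0.5 | r = 0.8 | r = 0.9 |
|---|---|---|---|---|
| Four interaction tests (the specified test) | 18% | 16% | 12% | 10% |
| All 12 pairwise tests, ungated (4 outcomes × 3 pairs, pooled variance) | 40% | 34% | 26% | 21% |
| Eight hypothesised pairs, ungated, either direction | 31% | 27% | 20% | 17% |
| Combined arm falsely better than either comparator on any outcome, ungated | 17% | 14% | 10% | 9% |
| Combined arm falsely better than both comparators on the same outcome | 1.8% | 1.7% | 1.3% | 1.0% |

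Testing pairs only after a significant interaction on the same outcome gives the first row again. If the two MAL subscales were tested separately, five independent interaction tests would give 1 − 0.95⁵ = 22.6%.

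**3. What the mixed ANOVA protects.** On one outcome, three ungated pairwise tests give about a 12% chance of a false difference. Requiring the interaction to be significant first brings this to 5%. That protection works among arms within one outcome. Across four outcomes the error is still the 10–19% of step 2.

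**4. Two ways to repair it.** With one named primary outcome at .05, λ stays at 10.5 and power at 0.803. With four co-equal outcomes under Bonferroni, α = .05/4 = .0125, power at N = 42 falls to 0.606, and 60 participants (20 per group) would be needed for 80%.

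**The case against.** The strongest objection concerns size. A reader might infer that four instruments and three arm pairs give about a one-in-three chance of a false claim of superiority. The protocol does not support that. It specifies the interaction test and names no pairwise test. One in three requires twelve ungated pairwise tests and an outcome correlation near 0.5–0.6. It also counts a difference in either direction between any two arms, including CIMT against control, which is not part of the hypothesis. A false result in favour of the combined arm against either comparator is about 9–17%, and against both on the same outcome under 2%. A larger figure that splits the WMFT into time and ability would also lack support, because the protocol defines only the 0–5 rating. These objections stand, and the figures here are limited accordingly.

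It can also be said that post hoc adjustment is commonly left to an analysis plan, which is not at hand, and that a threshold is not a statement that P values go unadjusted. That is fair for comparisons between arms. It does not settle the outcomes. The article has a full section and table on them, powers the trial without saying on which one, fixes .05 for everything, and uses one label for two scales. Those are features of the text as it stands.

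Lastly, the reassurance about the mixed ANOVA is reasonable for arms within an outcome. It does not reach across instruments.

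**Conclusion.** The point holds in this form. The success criterion is not fixed, because no outcome is primary and 'motor function' denotes two instruments. Under the stated rule, the four specified interaction tests carry about a 10–19% chance of at least one false positive, two to nearly four times the nominal 5%. If all arm pairs were also tested ungated, the range would be about 21–40%, but that is a conditional figure and not what the protocol describes. The ranges rest on an assumed common outcome correlation of 0.9 to 0 and on valid individual-level tests. With one center per arm, arm and center cannot be separated, so the actual error of each test may differ from 5%. That is a separate matter, and these percentages are not the trial's true error rate.

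**What to change.** Before analysis:

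1. Name one primary outcome. The WMFT is one example, as the motor function measure in Table 3; the FMA-UE is also an entry criterion. The choice is the sponsor's.
2. Make the group-by-time interaction on that outcome, at .05, the primary test, and compare arm pairs only if it is significant.
3. Label the other instruments secondary, and report them with confidence intervals and without confirmatory claims of superiority.
4. Use 'motor function' for one instrument throughout.
5. Correct Strengths and Limitations to say that the ANOVA limits error among arms within an outcome, not across outcomes.

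**Cost.** Only wording changes. N = 42 and power 0.80 for the primary test are kept, whereas Bonferroni over four co-equal outcomes would cut power to about 0.61. Three instruments lose confirmatory status, including the MAL, although perceived use is part of the hypothesis.

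The 0.80 belongs to the interaction, not to the arm pairs. At λ = 10.5, if CIMT equals control, the chance of showing the combined arm better than both is about 66%. If the three arms are evenly spaced, the chance for combined against CIMT is about 35%. Replacing the interaction with two adjusted contrasts would therefore need its own power check.

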### Recruitment and Randomization

Participants will be recruited from the NASAM. Three NASAM centers will be randomly assigned to 1 of 3 groups: the CIMT combined with the NMES group, the CIMT-only group, or the control group. Due to the specific nature of the therapies and the distinct characteristics of the centers, randomizing individual participants within centers is impractical. A cluster randomization approach will be used to minimize contamination among patients attending the same center. In addition, to minimize the risk of contamination between intervention groups, a cluster randomization approach will be used, wherein health care centers will serve as the unit of randomization. Each participating center will be randomly allocated to 1 of the 3 intervention arms using a computer-generated sequence administered by research personnel not involved in intervention delivery or outcome assessment. This concealed allocation process ensures allocation concealment and methodological rigor. Following randomization, all eligible patients who have experienced a stroke attending a given center will receive only the intervention protocol assigned to that facility. This methodological approach enables consistent intervention delivery within each site while substantially reducing the likelihood of cross-contamination between intervention groups—a critical consideration when evaluating health care provider–delivered rehabilitation protocols with behavioral components.

Eligible participants will provide written informed consent before their involvement in the study. The principal investigator or a trained research staff member not involved in therapy delivery will be responsible for obtaining consent from each participant. This process will take place only after participants have received a comprehensive explanation of the study procedures, ensuring that they clearly understand their involvement and the associated risks and benefits.

Following the informed consent process, baseline demographic information, including the participants’ names, ages, and gender, will be collected. Once demographic data have been obtained, the remaining baseline assessments will be conducted. Throughout the study, the confidentiality of all participants’ personal information and data will be strictly maintained in accordance with established research ethics guidelines and data protection regulations.

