### Therapist Training and Standardization

Recognizing that therapist-related variability represents a significant potential source of bias in rehabilitation trials, we have developed comprehensive standardization procedures to minimize therapist-level confounding. While the complete elimination of therapist effects remains impossible in hands-on interventions, our multifaceted approach ensures maximum consistency across sites and health care providers.

All participating therapists must complete a 3-day training program before commencing study treatments. This standardized curriculum encompasses theoretical foundations underlying each intervention approach, extensive hands-on skill development with practice participants, and a detailed review of all protocol procedures. Competency assessment requires therapists to achieve a minimum score of 90% on written examinations covering theoretical knowledge and protocol specifications and satisfactory performance on practical skills assessments evaluated by master trainers. Weekly refresher sessions throughout the trial will maintain intervention quality, address emerging questions, and ensure continued protocol adherence.

To enhance baseline comparability across sites, participation is restricted to therapists possessing at least 5 years of stroke-specific rehabilitation experience. This requirement ensures foundational clinical expertise while creating greater homogeneity in health care provider characteristics. Each therapist will exclusively deliver 1 intervention type throughout the study, eliminating within-center variability and reducing contamination risk between treatment arms. The same therapist will treat all participants within their assigned center, maintaining consistency in intervention delivery style and therapeutic relationship development.

Structured peer observations using standardized feedback forms will maintain consistent intervention quality across sites. Detailed session plans specifying exercise sequences, progression criteria, and acceptable modifications will limit unwanted variability while preserving necessary clinical flexibility for individual participant needs. This comprehensive standardization approach minimizes therapist-related variability while enabling appropriate statistical control for unavoidable health care provider effects, strengthening our trial’s internal validity and interpretability.

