### Strengths and Limitations

This trial incorporates several methodological strengths that enhance scientific rigor and clinical applicability. Blinded outcome assessors evaluate all participants using validated instruments spanning the International Classification of Functioning, Disability, and Health framework, ensuring a comprehensive assessment of motor impairment, activity limitations, and participation restrictions. Our standardized intervention protocols, supported by detailed treatment manuals and competency-based therapist training, promote consistent implementation across sites. The pragmatic trial design, conducted within existing rehabilitation centers using available clinical resources, enhances external validity and facilitates future implementation.

We acknowledge specific limitations inherent in our study design. While pragmatically necessary given resource constraints, the single-cluster-per-arm randomization strategy prevents traditional design effect calculations in our sample size calculation. We have addressed this limitation through conservative effect size selection and comprehensive statistical modeling that includes the center as a fixed effect covariate. Our mixed ANOVA approach protects against type I error inflation while maintaining adequate sensitivity for detecting clinically meaningful differences. The absence of long-term follow-up assessments limits our understanding of treatment durability; however, immediate postintervention outcomes will establish the foundation for future longitudinal investigations.

Despite rigorous standardization procedures, therapist-delivered interventions inevitably introduce some variability. We minimize this concern through mandatory competency assessments and structured fidelity monitoring. These mitigation strategies ensure that observed treatment differences reflect intervention efficacy rather than health care provider variability.

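### With one center per arm, the planned center fixed effect is a copy of treatment arm: it adjusts for nothing, and the claims of center control and valid inference that rest on it are unsupported

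*Protocol article*

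**What the plan says.** **Design.** Recruitment and Randomization states: "Three NASAM centers will be randomly assigned to 1 of 3 groups", and later "Each participating center will be randomly allocated to 1 of the 3 intervention arms". Patients "attending a given center will receive only the intervention protocol assigned to that facility". Table 2 lists one center for each arm. Strengths and Limitations confirms it: "the single-cluster-per-arm randomization strategy prevents traditional design effect calculations in our sample size calculation".

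**Model.** Statistical Analysis plans "linear mixed-effects models that include the center as a fixed effect covariate and random intercepts at the participant level" to deal with remaining center effects without a design effect. It adds: "This modeling framework accommodates hierarchical data structures in single-cluster designs while preserving valid inference for group-by-time interactions".

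**Claims resting on the model.**
- Therapist Training and Standardization describes its procedures as "enabling appropriate statistical control for unavoidable health care provider effects".
- Strengths and Limitations says that the single-cluster limitation was handled partly by "comprehensive statistical modeling that includes the center as a fixed effect covariate", and that the mixed ANOVA guards against an inflated type I error rate.
- Conclusions describes the modeling as suited to the clustering.

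**Providers.** Therapist Training and Standardization has one therapist treating everyone in a center and giving one intervention only. The text before Table 2 has the principal researcher and health care professionals giving sessions in all groups, and Table 2 shows the same delivery for each arm. Blinding asks therapists not to share their regimen with colleagues in their own or other centers, which implies more than one therapist per center.

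**The concern.** A covariate can adjust a treatment comparison only if it varies within treatment arms. Here center does not vary within any arm, so the term named as the remedy for center effects has no information to use. What would bias the group-by-time test is a center influence on change, and in these data that is the same quantity as the arm-by-time effect.

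Readers of the results would take the comparison as center-adjusted and its P value as valid for a cluster design. Neither would be true, and no analysis plan written later can make the term estimable. This is a stated property of the model that is wrong, not a detail left out of an article.

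**Working it through.** **1. Inputs from the protocol.** 3 centers and 3 arms, one center per arm; 42 participants, 14 per arm; 2 assessments (baseline and postintervention); α = 0.05, power 80%, effect size f = 0.25, within-between interaction test. No within-person correlation and no ICC are given.

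**2. The plan's own figure.** For this test, with k = 3 groups and m = 2 times:
- λ = f²·N·m/(1 − ρ), df1 = (k − 1)(m − 1) = 2, df2 = (N − k)(m − 1).
- Assuming ρ = 0.5 and ε = 1, N = 42 gives λ = 0.0625 × 42 × 2/0.5 = 10.5 and df2 = 39, with power 0.803. N = 39 gives 0.769.

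So 42 reproduces as an individually randomized calculation with no allowance for clustering. It depends on the assumed ρ: 81 at ρ = 0, 60 at 0.3, 27 at 0.7.

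**3. Does the center term add anything?** Fixed-effects design matrix for 42 participants × 2 times, with center equal to arm:

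| Model | Columns | Rank |
|---|---|---|
| arm × time | 6 | 6 |
| + center | 8 | 6 |
| + center + center × time | 10 | 6 |

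The two center columns repeat the two arm columns. Least-squares fitted values with and without center agree to about 4 × 10⁻¹⁶. A mixed-model fit with both terms stopped with a singular matrix; software that continues has to drop the redundant terms or set them to zero. Either way, what can be fitted is the arm × time model.

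**4. What the baseline measurement does.** In a simulated data set, shifting two centers' levels by +5 and −3 at both times left both arm-by-time estimates unchanged (0.437 and 0.054). A constant level difference therefore cancels, in a model without any center term.

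**5. What is left.** Suppose centers differ in mean change, with ICC the between-center share of the variance of change. With two times, the group-by-time test is a one-way ANOVA on change scores. With n = 14 per center, its F statistic is inflated under the null by

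1 + n·ICC/(1 − ICC),

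so the actual type I error is P{F(2,39) > F₀.₉₅(2,39)/[1 + 14·ICC/(1 − ICC)]}.

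| Assumed ICC of change | Inflation of F | Actual type I error |
|---|---|---|
| 0 | 1.00 | 5.0% |
| 0.01 | 1.14 | 7.1% |
| 0.02 | 1.29 | 9.4% |
| 0.05 | 1.74 | 16.9% |
| 0.10 | 2.56 | 29.3% |

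A simulation of 20,000 trials gave 16.9% at ICC 0.05 and 5.2% at ICC 0. The center term changes none of these figures. The calculation is for the model without patient covariates.

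**The case against.** The strongest reply has four parts.

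- **The model still does useful work.** This stands. The participant random intercept handles within-person correlation, and baseline motor function and stroke severity adjust for measured patient differences. A reader might infer that the whole mixed model adjusts for nothing, or that the result is a raw difference between three centers. The protocol supports neither reading: only the center term is empty, and the target is a difference in change.
- **Provider differences are controlled.** This stands in part. Training, the 90% examination threshold, the experience minimum, manuals, identical kits and the audit of 20% of sessions may reduce them by design. What the model does not supply is statistical control.
- **Therapist is not simply arm.** This stands. A reader might infer from Therapist Training and Standardization that center, therapist and arm are one variable. The Blinding section and the text before Table 2 point to several providers per center and a principal researcher who treats in every arm. Provider influence on change is confounded only to the extent that providers do not cross arms, and these passages conflict. Center equals arm whichever is right.
- **The limitation is disclosed.** This stands only in part. Strengths and Limitations names the single-cluster design, and the text on future directions calls for trials with proper design effects. But the disclosure presents it as an obstacle to sample size calculation, then says that it was addressed, in part by the empty term. Nowhere does the protocol say that center and arm coincide.

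**Conclusion.** The point holds for the center term and must be corrected. That center duplicates arm follows from the stated design and needs no outside figure: the term contributes no estimable parameter, and zero degrees of freedom remain to separate arm from center. Any center influence on change is fully confounded with the arm-by-time effect.

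The claims of handling center effects, valid group-by-time inference, statistical control of providers, a resolved single-cluster limitation, type I error protection and cluster-suited modeling are therefore unsupported.

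The size of the harm is conditional. Type I error stays at 5% if centers do not differ in change, and is about 7%, 17% or 29% at assumed ICCs of 0.01, 0.05 or 0.10. With one center per arm, the trial's own data cannot show which applies.

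**What to change.** 1. In Statistical Analysis, delete the center covariate and the statements that the model handles center effects and keeps group-by-time inference valid. Keep the participant random intercept and the patient covariates.
2. Delete or correct the dependent claims: statistical control of providers (Therapist Training and Standardization), the resolved single-cluster limitation and type I error protection (Strengths and Limitations), and cluster-suited modeling (Conclusions).
3. Insert a statement along these lines: Center is completely confounded with arm, and no center adjustment is possible. The arm-by-time contrast estimates the intervention effect plus any effect of center, and of providers who do not cross arms, on change. P values and confidence intervals are conditional on no between-center difference in change.
4. Reconcile the accounts of who delivers treatment in Blinding, in Therapist Training and Standardization, and around Table 2, so that the provider part of that statement can be made definite.
5. Optionally, report the group-by-time test over a range of assumed between-center variances of change, as in the table above.

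This changes wording and needs no new data. The group-by-time estimate and test stay the same, but what may be concluded from them becomes less favorable. Separating intervention from center would need several centers per arm or randomization within centers, which is a change of design.
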